## Abstract

**Background:**

Acute gouty arthritis (GA) is the main clinical manifestation and the most common initial symptom of gout. The treatment of acute GA involves the use of colchicine, non-steroidal anti-inflammatory drugs, and corticosteroids. Because of the side effects of these drugs, their clinical applications are limited. The use of traditional Chinese medicine for the treatment of acute GA has unique advantages. The aim of this trial is to clarify the treatment efficacy, safety, and recurrence control efficacy of *Huzhang* granules (HZG) in patients with GA showing dampness-heat syndrome.

**Methods/design:**

This double-blind, randomized, controlled trial was planned to be conducted between July 1, 2020, and December 31, 2022. A sample size of 267 participants (89 per group) with GA will be randomly assigned to three treatment groups in the ratio of 1:1:1: HZG, etoricoxib, and placebo groups. The study duration is 13 days, including a 1-day screening period, 5-day intervention period, and 1-week follow-up period. The primary outcome is analgesic effectiveness, assessed as pain in the worst-affected joint, which will be measured using the visual analog scale. Secondary outcomes include the patient’s assessment of pain in the primary study joint, patient’s global assessment of response to therapy, investigator’s global assessment of response to therapy, investigator’s assessment of tenderness and swelling of the study joint, and TCM syndromes. Furthermore, the number, nature, and severity of adverse events will be recorded.

**Discussion:**

This study will provide evidence regarding the clinical efficacy and safety of Chinese medicine treatment for acute gouty arthritis. This study will provide noteworthy findings.

**Trial registration:**

ClinicalTrials.gov NCT04462666. Registered on July 05, 2020 (first version).

## Background

Gout is a recurrent chronic inflammatory disease caused by monosodium urate (MSU) crystals [1]. Acute gouty arthritis (GA) is the most common symptom of gout. The frequency of acute attacks increases with disease progression, and joint destruction may occur [2, 3]. The pooled prevalence of hyperuricemia in China from 2000 to 2014 was approximately 13.3%, and the pooled prevalence of gout was 1.1%; hyperuricemia seriously affects the quality of life, resulting in large economic costs and mental stress [4]. Healing gout is often an unachieved goal [5–7].

Acute GA is the main reason that patients with gout visit a doctor. The main pathological change is acute inflammation of the joint and its surrounding tissues caused by the precipitation of MSU crystals [8]. The treatment of acute GA involves the use of colchicine, non-steroidal anti-inflammatory drugs (NSAIDs), corticosteroids, or a combination of any two agents [9]. For severe refractory GA, anti-tumor necrosis factor-α or anti-interleukin-1β monoclonal antibodies can be used [10, 11]. However, these agents are associated with severe potential adverse effects (AEs) and risk of drug–drug interactions, especially in elderly patients and those with chronic renal insufficiency or diabetes [12]. In addition to these conventional treatments, traditional Chinese medicine (TCM) has attracted considerable attention because of its efficacy and low incidence rates of side effects [13, 14].

The use of TCM for the treatment of GA has been associated with satisfactory therapeutic effects, with fewer AEs and minimal toxicity [15]. In TCM, GA belongs to the Bi pattern category, and the primary cause is the invasion of wind, cold, dampness, heat, or other pathogenic factors. Among these factors, dampness and heat are the most common external causes of GA. The main TCM treatments for GA include clearing heat and removing dampness, as well as promoting blood circulation and removing blood stasis [15]. The modified Simiao decoction has demonstrated effectiveness in the treatment of GA by eliciting anti-inflammatory effects and lowering urate levels [16].

*Huzhang* granules (HZG), a Chinese herbal prescription, are composed of 12 ingredients (*Polygonum cuspidatum*, *Notopterygium*, *Angelicaepubescentis*, *Angelica*, *Ligusticum wallichii*, *Rhizomaatractylodis*, *Cortex phellodendri*, *Bidentate achyranthes*, *Capillary wormwood*, *Stephania tetrandra*, *Tuckahoe*, and *Cynanchumpaniculatum*) (Table 1). The predecessor of HZG is the *Huzhang Tongfeng* decoction, which was formulated in the 1980s by [name] (a well-known Chinese surgeon) and has been used in the clinical treatment of gout for over 30 years at the Yueyang Hospital of Integrated Traditional Chinese and Western Medicine affiliated to Shanghai University of TCM. According to the syndrome differentiation approach in TCM, there are four syndromes of GA: wind-dampness-heat, damp-turbidity, blockage of phlegm and blood stasis, and chronic obstruction due to deficiency. These four syndrome types correspond to the four stages of GA: acute stage, remission stage, chronic stage, and later stage. The method of clearing heat, removing dampness, and dredging collaterals is generally used for the treatment of acute GA [14, 16]. HZG was composed on the basis of this method.

**Table 1 Tab1:** Ingredients of *Huzhang* granules (intervention drug) with English translations

Main composition	Latin scientific name	Plant part	Amount (g)
*Polygonum cuspidatum*	*Reynoutria japonica Houtt.*	Rhizome	15
Notopterygium	*Notopterygiumincisum Ting ex H. T. Chang*	Rhizome	9
Angelicaepubescentis	*Heracleum hemsleyanum Diels*	Rhizome	9
Angelica	*Angelica sinensis (Oliv.) Diels*	Root	12
Ligusticumwallichii	*Ligusticum chuanxiong Hort.*	Rhizome	10
Rhizomaatractylodis	*Atractylodes Lancea (Thunb.) DC.*	Rhizome	12
Cortex phellodendri	*Cortex Phellodendri Chinsis*	Bark	12
Bidentate achyranthes	*Achyranthes bidentata Blume.*	Root	12
Capillary wormwood	*ArtemisiacapillarisThunb.*	Stem and foliage	15
Stephania tetrandra	*Stephania tetrandra S. Moore*	Root	9
Tuckahoe	*Poria*	Sclerotium	15
Cynanchumpaniculatum	*Cynanchumpaniculatum (Bunge) Kitagawa*	Root and rhizome	15

Our data from clinical studies confirm the effectiveness of HZG in the treatment of GA, with 87.5% of the patients showing improvement in joint swelling and pain. Moreover, HZG can significantly reduce white blood count, erythrocyte sedimentation rate, and C-reactive protein and interleukin-6 levels in patients with GA [14]. However, because of the complex composition of HZG, the mechanism underlying its therapeutic action remains unclear.

The beneficial effects of HZG on acute GA are well known and are considered to be derived from the improvement of wind-dampness-heat syndrome, leading to improvement of joint inflammation. However, no large-scale randomized controlled trials have been conducted on the efficacy, safety, and recurrence control efficacy of HZG. Therefore, we aim to conduct a double-blinded, randomized, controlled clinical trial to evaluate the efficacy of oral HZG for the treatment of patients with acute GA showing wind-dampness-heat syndrome.

## Methods

### Design

This study is designed as a three-parallel group, double-blind, randomized, controlled clinical trial. The objective is to clarify the clinical efficacy, safety, and recurrence control efficacy in patients with wind-dampness-heat syndrome. The research findings will be applied to establish a clinical standard for the treatment of gout. At the time of the writing of the trial protocol (version 1.0, April 09, 2020), enrollment for the trial was yet to begin. Recruitment was expected to start on July 1, 2020, and end on December 31, 2022.

We aim to recruit individuals from the Shanghai region, China. Patients with acute gout requiring primary and secondary care, including inpatients who develop an acute gout attack, will be recruited. Recruitment will occur in the secondary care setting with treatment occurring on an outpatient basis, or it can occur in secondary care if symptoms warrant admission or if the participant is already an inpatient and develops an acute gout attack. A total of 267 people will participate in this clinical trial, and each participant can only be enrolled once. The study will be conducted at the Shanghai Yueyang Integrated Medicine Hospital.

The study consists of five phases: screening/enrollment, allocation, treatment/intervention, end of intervention, and follow-up. In the enrollment process, participants will be recruited via a gout specialist clinic for physical examination and eligibility assessment. The time between assessment and intervention should not exceed 1 week (week 0). If more than a week has passed since the assessment, the assessment of the participant will be repeated before the intervention. If eligible, the participants will be requested to sign the written informed consent regarding participation in the trial (procedures, risks, options for dropping out), the use of laboratory data, and collection, storage, and use of biological specimens. Details of informed consent will be explained by the study investigators or medical staff members with adequate training. Once an informed consent form is signed and dated by the participant, a participant identification number will be assigned to facilitate participant identification.

Participants will be randomly allocated to HZG, etoricoxib, or placebo groups and undergo corresponding intervention over the course of the 5-day treatment period. We will treat the participants in the HZG group with HZG and etoricoxib placebo tablets, those in the etoricoxib group with etoricoxib tablets and HZG placebo, and those in the placebo group with HZG placebo and etoricoxib placebo tablets (Fig. 1). The participants will receive systemic therapy according to the judgment of their treating physicians. We will record all changes in symptoms, prescriptions, relevant scores, macroscopic characteristics (based on photographic evidence), and any AEs. This placebo-controlled study will verify whether the curative effect of HZG is better than that of a placebo, which will adequately test the efficacy of HZG. This study design applied in such a validation is superior.

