### Eligibility criteria

Inclusion criteria:
(i) Diagnosis of acute gout arthritis as defined by the American College of Rheumatology 1977 preliminary criteria,(ii) Male or non-pregnant, non-nursing female individuals,(iii) 18–70 years of age,(iv) Occurrence of gout attack ≤ 48 h previously,(v) In the week before this observation, non-steroidal anti-inflammatory drugs, analgesic, drugs, and drugs affecting uric acid metabolism were not used,(vi) Subjects capable of providing informed consent,

Exclusion criteria:
(i)Failure to meet diagnostic criteria,(ii)Evidence of uncontrolled concomitant cardiovascular, neurological, hepatic, or gastrointestinal disease—potential participants who have active concomitant disease can only be eligible after discussion and agreement with the treating medical team,(iii)Patients in a critical condition that makes it difficult to evaluate the effectiveness and safety of clinical observations,(iv)Severe deformity, stiffness, and labor loss in patients with advanced arthritis,(v)Known allergy to drugs used in this study.

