### Treatment cycles

The treatment is planned for 5 days in one cycle. All interventions will be stopped after the 5-day treatment period and 1-week of follow-up.

The pain associated with acute GA is self-limiting; that is, it can resolve on its own after approximately 1 week without medication. The participants will be informed on the consent form that if they cannot bear the pain, they can withdraw from the study at any time and choose other treatment options.

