## Discussion

GA is caused by the deposition of MSU crystals in soft tissue, triggering severe but self-limited bouts of acute arthritis accompanied by intense pain, as well as articular and periarticular inflammation [19]. The acute attack of gout not only causes joint pain and dyskinesia, but more importantly, gout is associated with a number of complications, including hypertension, chronic kidney disease, cardiovascular disease, obesity, insulin resistance, diabetes, and hyperlipidemia [20–22].

In the early stages, gout often manifests as intermittent acute arthritis. A single joint is mainly involved, most commonly the first metatarsophalangeal joint. Joint swelling and pain usually last for 7 days, can be spontaneous or relieved by drugs, and do not have any symptoms during the interval [22]. With the extension of the course of gout, the number of attacks and the number of joints involved gradually increase, and joint symptoms begin to appear during the interval [23]. At the same time, the tophus is formed in the joint, skin, and soft tissue, and the joint is damaged or even maimed. Although gout treatment is effective, the compliance of patients with gout is unsatisfactory [24]. Poor compliance not only directly affects the therapeutic effect on patients but also places a heavy burden on the entire medical and health department [25–28].

TCM has been used for the treatment of gout for a long time, and its curative effect is remarkable. TCM considers that GA is caused by internal and external causes; the external causes mainly include wind, cold, dampness, and heat, while the internal causes mainly include the deficiency of vital *qi* of the human body, disorder of ascending clear and descending turbid function of spleen and kidney, and deficiency of *qi* and blood, leading to dampness-heat, turbid phlegm, stagnation of blood stasis, spleen deficiency, and other syndromes [29, 30], among which dampness-heat syndrome is the most common cause. Based on clinical practice, combined with the TCM-based pathogenesis of GA, our research group has formulated the TCM prescription of HZG, which is used to treat GA on the basis of the treatment principles of clearing heat, removing dampness, and dredging collaterals.

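### The one-week allowance between assessment and intervention contradicts the 48-hour onset criterion, the 1-day screening period and the Day 0 to Day 1 schedule

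*Protocol article*

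**What the plan says.** Four parts of the protocol article bear on how old an attack may be when treatment starts.

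- **Design:** "The time between assessment and intervention should not exceed 1 week (week 0", and then "If more than a week has passed since the assessment, the assessment of the participant will be repeated before the intervention".
- **Eligibility criteria, inclusion (iv):** "Occurrence of gout attack ≤ 48 h previously". The criterion does not say whether the 48 hours run to assessment, randomisation or first dose.
- **Abstract, Methods/design:** "The study duration is 13 days, including a 1-day screening period, 5-day intervention period, and 1-week follow-up period".
- **Table 2:** screening is on Day 0 and treatment runs from Day 1. Eligibility screening is marked under Screening/enrolment and again under Allocation.

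Randomization and allocation adds that staff confirm eligibility in the web system when the patient is randomised.

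On the natural course of the attack, Treatment cycles says of the pain that "it can resolve on its own after approximately 1 week without medication", and the Discussion says "Joint swelling and pain usually last for 7 days". The primary endpoint (Primary outcome) is joint pain on treatment days 2–5.

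**The concern.** The 48-hour criterion makes sense only if treatment follows quickly, because the disease resolves on its own. A rule that tolerates a week between assessment and intervention does not fit it. The repeat-assessment rule does not fit either: a patient re-assessed after more than a week cannot meet a 48-hour limit for the same attack. The repeat could readmit that patient only if the limit were not re-applied or a new attack had begun.

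What is at stake is the trial's ability to separate the arms. A patient whose attack is over, or nearly over, has little pain left for any treatment to reduce. Such patients would pull both *Huzhang* granules against placebo and etoricoxib against placebo towards no difference.

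**Working it through.** **Inputs, all from the protocol article**

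- Maximum attack age under inclusion (iv): 48 h = 2 days, taken here as counted at assessment (the criterion does not say).
- Maximum gap from assessment to intervention (Design): 7 days.
- Screening, treatment and follow-up (abstract): 1, 5 and 7 days.
- Natural duration of an attack (Treatment cycles, Discussion): about 7 days.
- Endpoint window (Primary outcome): treatment days 2–5, with day 1 the day of first dose.

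**Stated study duration**

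1 + 5 + 7 = 13 days, which reproduces the abstract. If the full week before intervention is used, the total is 7 + 5 + 7 = 19 days, which does not fit 13.

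**Attack age at first dose and in the endpoint window**

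For a patient assessed at the full 48 hours:

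- attack age at first dose = 2 + gap
- endpoint window = (attack age at first dose + 1) to (attack age at first dose + 4)

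| Gap, assessment to first dose | Attack age at first dose | Treatment days 2–5 fall at |
|---|---|---|
| 0 days | 2 days | 3–6 days after onset |
| 1 day (abstract, Table 2) | 3 days | 4–7 days |
| 2 days | 4 days | 5–8 days |
| 5 days | 7 days | 8–11 days |
| 7 days (Design limit) | 9 days | 10–13 days |

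On the 1-day path, the endpoint window lies within the stated natural duration. At the Design limit, all of it lies beyond. For this patient the first dose itself passes day 7 once the gap exceeds 7 − 2 = 5 days. A patient assessed earlier in the attack needs a longer gap: one assessed at onset would need more than 7 days, which the Design section already sends to re-assessment.

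**Does any passage settle the conflict?**

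Design is the only section that sets an explicit limit on the interval from assessment to intervention. Table 2 and Randomization and allocation place an eligibility check at allocation. Neither says whether that check re-times the attack against 48 hours or confirms a decision made at assessment. Inclusion (iv) names no reference point. The text therefore leaves the conflict open.

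**The case against.** The strongest reply is that the article does provide a second eligibility check, in Table 2 at Allocation and in the web system at randomisation. Outcomes are timed from randomisation, the first at 4 hours, which implies that dosing follows closely. If onset is re-timed at that check, a late start is blocked. The one-week sentence can also be read as an outer limit that leaves every inclusion criterion in force. Baseline VAS is marked at Allocation too, so a resolved attack would be visible.

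Much of this stands. A reader might infer from the Design section that patients can start late with no re-assessment, or that the one-week rule overrides the 48-hour limit. The documents support neither: the first is true of the Design section taken alone, and nothing says that its interval suspends an inclusion criterion. The 9-day case is also an extreme corner, needing assessment at the full 48 hours, a full 7-day gap and no onset check at randomisation. Nothing suggests that such delays are planned or have happened.

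The reply does not remove the contradiction. No passage says that the 48 hours are re-applied at allocation. The baseline VAS would show a resolved attack, but the listed criteria contain no minimum pain score that would exclude it. If the allocation check does enforce 48 hours, the one-week allowance and its repeat rule cannot operate as written.

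**Conclusion.** The contradiction is real and should be corrected. The Design rule conflicts with inclusion (iv), the 1-day screening and 13-day duration, and the Day 0 to Day 1 schedule. Its size in time follows from the article's own figures: up to 9 days from onset to first dose instead of about 3, and an endpoint window at about 10–13 days instead of 4–7. This assumes that 48 hours is counted at assessment and that allocation does not re-apply it.

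The direction of the effect, smaller differences between all arms, follows if late starters have little pain left. Its size cannot be given. A reader might want to turn this into a loss of power, but the article gives no late-start rate, and any such figure would rest on an invented fraction. This is an inconsistency that could blunt the primary endpoint, not evidence that it has done so.

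**What to change.** 1. Reconcile the abstract, Design, inclusion (iv), Randomization and allocation, and Table 2. State the time point to which the 48 hours refer, and make the assessment-to-intervention interval and the re-assessment rule consistent with it. Which limit applies is for the sponsor and investigators to decide.
2. Say what the eligibility check at allocation covers, in particular whether attack onset is re-timed there.
3. Record the time from onset to randomisation for every patient, retrospectively where available for the 145 reported as recruited under Trial status. At that count, up to 267 − 145 = 122 patients were still to be enrolled and could be covered prospectively.
4. Use that record to make possible a sensitivity analysis limited to patients inside the window. Onset-to-randomisation time is fixed before allocation, so restricting on it does not select patients on anything that treatment could influence. The analysis plan is not shown, so this is a use for the data and not a claim that an analysis is missing.

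The cost is a short amendment, a data field and some retrospective source checking for those already recruited. If the reconciled rule is the tighter one, a few late patients become ineligible.

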### Measurements

Demographic data such as age, sex, ethnicity, race, and body mass index will be recorded. Individuals will receive the following instructions during the trial period: no alcohol, low-purine, low-fat diet, and plenty of water (≥ 2000 ml/day); avoid predisposing factors such as joint cold, trauma, and excessive fatigue; and avoid use of diuretics, salicylic acid preparations, glucocorticoids, and other drugs that affect uric acid metabolism and excretion. Before the beginning of treatment and after 5 days of treatment, medical histories will be recorded for each patient, and laboratory examinations will be performed and will include the following: C-reactive protein, interleukin, blood routine, blood biochemistry, routine urine test, and electrocardiogram. In addition, the tenderness, redness, and swelling of the involved joint, symptom relief time, patient satisfaction, and 36-Item Short Form Survey values will also be collected. The study team will build and maintain electronic case report form data and ensure data completeness and quality periodically by means of internal audits. Double data entry will be used to ensure data quality. All efforts will be made to maintain confidentiality of patient data by using multiple means, such as de-identification, use of password-protected secure servers, and restriction of access to study team members.

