### Drug combination

In this study, all drugs will be considered as combined drugs. Details including trade name, dosage, indications, and duration of medication will be recorded in the case report form. Whether a participant should withdraw from the trial because of the nature of the combined drugs will be judged by the study investigators. The use of diuretics, salicylic acid preparations, glucocorticoids, and other drugs that affect uric acid metabolism and excretion will be avoided.

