Previous research indicated that HZG has an anti-inflammatory effect on the downregulation of NALP3 and caspase-1 at the protein translation level [31]. Based on these previous observations, we cultured fibroblast-like synoviocytes stimulated by MSU with serum containing HZG and found that HZG inhibited the expression of IL-1β, TNF-α, and IL-6 [14]; this supports the therapeutic effect of HZG in patients with GA showing dampness-heat syndrome and motivated us to initiate this trial.

In this trial, we will use the granule formulation to minimize deviations associated with the use of herbs from different geographical regions, different varieties, and maintained under different storage conditions. We chose etoricoxib as a comparative drug. Etoricoxib is a new cyclooxygenase-2 (COX-2) inhibitor that can be used in the treatment of GA. The 2012 American College of Rheumatology guidelines for the management of gout indicate that etoricoxib has an evidence-based grade of A in the treatment of GA when using COX-2 inhibitors [32]. In this study, we aimed to clarify the efficacy of HZG treatment twice daily for 5 days. As acute GA is prone to recurrence, we emphasize a 1-week follow-up after the end of treatment.

We will carefully monitor the recurrence after the end of GA treatment. In addition, we will record all AEs and information regarding concomitant medications at each visit. The study results will help clarify the efficacy of HZG, as well as its safety in the treatment of GA in terms of both inflammation regression and rate of recurrence. We expect that this study will provide high-quality evidence that can be used to develop clinical treatment guidelines. Therefore, the results of this study are expected to have an important impact on public health.

The limitations of the study should be mentioned. Only one trial drug regimen will be tested, and the prescription will not be adjusted according to symptoms, which means that the results may be specific to the test regimen. In addition, because of the reliance on etoricoxib as the control drug in our study, our findings may not apply to the adverse reactions of other NSAIDs. Nevertheless, the findings will still be useful as a reference in clinical practice and will help pave the way for future research. Finally, the HZG prescription to be used in this trial was designed for the treatment of GA with dampness-heat syndrome; thus, the findings may not be applicable to other syndromes.

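### Open-ended, physician-chosen systemic therapy during the 5-day treatment period is not reconciled with the protocol's other drug rules and can dilute the HZG–placebo comparison

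*Protocol article*

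**What the plan says.** All references are to the protocol article.

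- **Design**, in the paragraph on the 5-day intervention: "The participants will receive systemic therapy according to the judgment of their treating physicians". The same paragraph gives HZG against placebo as the comparison that tests efficacy.
- **Measurements**, as an instruction to participants: "avoid use of diuretics, salicylic acid preparations, glucocorticoids, and other drugs that affect uric acid metabolism and excretion". **Drug combination** repeats the list: "The use of diuretics, salicylic acid preparations, glucocorticoids, and other drugs that affect uric acid metabolism and excretion will be avoided".
- **Drug combination** also treats all drugs as combined drugs and enters trade name, dosage, indication and duration in the case report form. It then adds: "Whether a participant should withdraw from the trial because of the nature of the combined drugs will be judged by the study investigators".
- **Treatment cycles**, on what participants are told: "if they cannot bear the pain, they can withdraw from the study at any time and choose other treatment options".
- **Secondary outcome** allows a patient to be withdrawn or put back on standard care, on clinical indication or at the patient's request.
- **Eligibility criteria**, for entry only: "In the week before this observation, non-steroidal anti-inflammatory drugs, analgesic, drugs, and drugs affecting uric acid metabolism were not used".
- **Background** gives colchicine, NSAIDs and corticosteroids as the treatments of acute gouty arthritis.
- **Primary outcome** places the endpoint on treatment days 2–5.
- **Statistical analysis** keeps all randomized patients in the ITT analysis, imputes by last observation carried forward (LOCF), and adds a per-protocol analysis.
- **Table 2** marks drug combination at allocation, Day 5 and end of intervention. The **Discussion** says "we will record all AEs and information regarding concomitant medications at each visit".

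**The concern.** The same event, a participant in pain who needs another drug, can lead to three different outcomes under this text: treatment within the trial, return to standard care, or withdrawal. Nothing says which applies when, and each affects the primary comparison differently.

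If the participant is treated and stays in, later pain scores partly reflect the other drug. Placebo participants plausibly have the most need of it, so the HZG–placebo difference shrinks. If the participant is withdrawn on an investigator's judgment, the remaining scores are filled by LOCF in the ITT analysis, and membership of the per-protocol set depends on a decision made after randomization. In either case the estimate depends on a practice that the protocol leaves undefined.

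**Working it through.** **1. The passages side by side**

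| Drug class | Restricted in the week before entry (Eligibility) | Named on the on-study avoid-list (Measurements, Drug combination) | Given as acute gout treatment (Background) |
|---|---|---|---|
| Glucocorticoids | not named | yes | yes (as corticosteroids) |
| Salicylates | not named as such | yes | not named as such |
| Other NSAIDs | yes | not named | yes |
| Analgesics | yes | not named | not named |
| Colchicine | not named | not named | yes |

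The Design sentence has no exception. For glucocorticoids and salicylates it conflicts, read literally, with the avoid-list. For other NSAIDs, analgesics and colchicine the avoid-list does not name them, so there is a gap rather than a contradiction.

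**2. Inputs for the size**

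From Sample size: response rates of 63.89% (etoricoxib), 42.5% (TCM, taken as HZG) and 15.5% (placebo); two-sided α 0.05; power 0.80; 74 per group, 89 enrolled.

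Formulas (pooled variance under the null, d = p₁ − p₂, p̄ = (p₁ + p₂)/2):

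- n = [1.96√(2p̄(1−p̄)) + 0.842√(p₁(1−p₁) + p₂(1−p₂))]² / d²
- power = Φ{[d√n − 1.96√(2p̄(1−p̄))] / √(p₁(1−p₁) + p₂(1−p₂))}

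**3. The plan's own figure**

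Taking 15.5% against 35.5% (placebo plus the stated 20 points; the 35.5% is inferred) gives n = 73.4, rounded up to 74. Then 74 × 1.2 = 88.8, rounded up to 89. Both stated figures reproduce.

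**4. HZG against placebo with no other therapy**

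d = 0.425 − 0.155 = 0.270. At n = 74, power = Φ[(2.323 − 1.258)/0.613] = 95.9%. At n = 89 it is 98.2%.

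**5. With other therapy**

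Assumption, not in the protocol: a fraction f of an arm takes effective non-trial therapy and then responds at the etoricoxib rate.

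- HZG rate = 0.425 + f_H × (0.6389 − 0.425)
- Placebo rate = 0.155 + f_P × (0.6389 − 0.155)

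Worked case, f_H = f_P = 0.2: the rates are 0.468 and 0.252, d = 0.216, and power at 74 = Φ[(1.858 − 1.330)/0.661] = 78.8%.

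| Use on HZG | Use on placebo | Difference (points) | Power, 74 per arm | Power, 89 per arm |
|---|---|---|---|---|
| 0% | 0% | 27.0 | 96% | 98% |
| 10% | 10% | 24.3 | 89% | 94% |
| 20% | 20% | 21.6 | 79% | 86% |
| 10% | 20% | 19.5 | 70% | 78% |
| 0% | 20% | 17.3 | 61% | 69% |
| 30% | 30% | 18.9 | 66% | 74% |
| 15% | 30% | 15.7 | 50% | 58% |
| 0% | 30% | 12.5 | 35% | 41% |

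**The case against.** The strongest reply is that systemic therapy may mean general care, with Measurements and Drug combination setting its specific limits. That reading is possible, but no sentence says so, and it would still leave NSAIDs, analgesics and colchicine unaddressed on study.

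Four stronger readings are tempting, and the protocol does not support them.

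- *Treatment cycles forbids other treatment within the trial.* It gives participants a right to leave ("they can withdraw from the study at any time and choose other treatment options"), and Drug combination expressly foresees other drugs. This is a tension, not a contradiction.
- *Other drug use cannot be placed in time.* Table 2 taken alone suggests this, but Drug combination records duration of medication, Design records changes in prescriptions, and Secondary outcome records combined medication during treatment. What remains is the mismatch between Table 2 and the Discussion.
- *The whole analysed population depends on investigators' choices.* The ITT set holds all randomized patients, and Termination and withdrawal seeks a final evaluation from those who leave. The problem is imputation in the ITT analysis and selection in the per-protocol set.
- *Power falls to 61% or 35%.* Those figures assume use on placebo only, which is the extreme case, since the Design sentence covers every participant. If use follows non-response (57.5% on HZG, 84.5% on placebo, ratio 0.68), 20% placebo use gives 74% power at 74 per arm and 81% at 89. At 30% use the figures are 56% and 64%.

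Two further points stand. The calculation uses response rates, as the sample size does, whereas the stated endpoint is pain on a visual analog scale (VAS). And counting first use as non-response is only one possible estimand, so it belongs in a sensitivity analysis here, not as a required primary rule.

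**Conclusion.** The concern holds in this limited form. The Design sentence is unlimited. Read literally, it conflicts with the avoid-list for two drug classes, and it leaves the other main treatments of acute gout unaddressed inside the primary endpoint window. Followed as written, the plan can weaken the comparison it names as its test of efficacy.

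The size is not known, because no usage rate is given. If users respond at the etoricoxib rate, 20% use in both arms is enough to bring 74 per arm just under the planned 80% power. With all 89 per arm in the analysis, power stays above 80% at equal 20% use, but falls to 78% when placebo use is twice HZG use and to 69% when it is on placebo only. These are conditional illustrations and do not predict what happened in the trial.

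**What to change.** 1. Reconcile Design, Eligibility criteria, Secondary outcome, Treatment cycles, Measurements and Drug combination into one statement of what non-trial therapy is possible on days 1–5. Its content is for the clinical team.
2. Align the drug-combination row of Table 2 with the recording at each visit stated in the Discussion, so that start and stop dates of any non-trial analgesic or anti-inflammatory drug can be set against the VAS scores. A new record cannot be applied backwards to the 145 patients already recruited at the time of the article; for them, use the case-report-form medication entries.
3. Report such use by arm.
4. Before unblinding, prespecify a sensitivity analysis beside the ITT analysis that treats pain after first such use as unfavourable (non-response).

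The cost is a wording amendment with notice to the ethics committee, a little more recording and one extra analysis. Response rates in that sensitivity analysis may look less favourable.
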